### Minimally acceptable intervention adherence rates

Adherence to diet will be closely monitored by the study team by measuring serum β-hydroxybutyrate levels once a week. A blood concentration of 0.5–3 mM (nutritional ketosis) will be considered safe and acceptable. Adherence will also be assessed using food records. The food record will be a simple checklist to indicate that supplied foods were consumed, with space to add the quantity of consumption and any deviations from the protocol. In addition, the study dietician will communicate directly with each participant at least weekly to improve adherence.

### Clinical procedures to measure safety

Fasting blood samples are collected to determine the levels of biomarkers of systemic inflammation, lipids, sodium, liver enzymes and glycemic status. In addition, blood samples are collected for measurement of blood ketone (β-hydroxybutyrate) levels three times a week, 2 h after the first meal of the day, to confirm nutritionally induced ketosis (blood concentration 0.5–3.0 mM) in the KD group. All serum samples will be obtained in the UAB Hospital Acute Care Unit and then stored in freezers within the PI’s ([name]) research laboratory at −80°C until analyzed by core personnel. Levels of sodium, β-hydroxybutyrate, lipids, C-reactive protein, glucose and insulin are assessed via enzymatic assays in the Diabetes Research Center Human Physiology Core. The concentration of low-density lipoprotein cholesterol is calculated using the Friedewald formula. In addition, levels of liver enzymes are measured via enzymatic assays at the UAB Hospital Outreach Laboratory.

### Procedures to measure neurological recovery

The motor and sensory examinations are performed according to the ISNCSCI standards [29–31] and described by AIS. The scales used for the neurological tests for this proposal were selected because they are standard, widely accepted tools and can be readily administered in the acute SCI setting. The AIS Motor Index Score is used for measuring motor function. This index uses standard manual muscle testing on a six-point scale (graded 0–5). The maximum motor score for upper and lower extremity is 50. For the sensory examination, each dermatome is tested for both sharp (pin-prick) and light touch sensation and sensory status is graded on a three-point scale. Numerically, the sensory scores total 116 points.

EPTs are recorded according to established standards [23]. In brief, electrical stimuli are delivered at 3 Hz at key points within cervical dermatomes (C4 to C8). Stimulation commences at 0 mA and progressively increase at 0.1-mA intervals until the participant perceives a stimulus. The stimulus is then turned down until perception is lost. This process is repeated three times to generate an average EPT for each dermatome.

### Procedures to measure functional independence

The SCIM is used for measuring functional independence [24, 25] and is, at present, the only comprehensive rating scale that measures the ability of patients with SCI to perform everyday tasks according to their value for the patient. It requires no manual testing and the range of the total score is 0–100. Although one American Spinal Injury Association In-Step certified clinician performs all examinations, inter-rater reliability between the primary examiner and back-up examiners are assessed periodically as a quality assurance measure for consistency and a precautionary measure in the event that a back-up examiner might be required. Examiners are blinded to the diet assignment. Neurological examinations are routine both in the acute and inpatient care (in the SRC) facilities under the supervision of physiatrist.

### Procedures to determine gut microbiome composition

Microbiome collection and analysis are performed using established protocols [18]. Briefly, stool samples are collected in ParaPak vials (Meridian Biosciences, Inc., Cincinnati, OH, USA) and consequently diluted to 0.1 mg/ml in Cary-Blair medium for a total volume of 20 ml with 10% glycerol (by volume). Aliquots of 5 ml are stored at −80°C in cryovial tubes until DNA extraction. Stool bacterial DNA is extracted using a Zymo Research Fecal DNA isolation kit (Zymo Research, Irvine, CA, USA) as per the manufacturer’s instructions. Polymerase chain reaction is then used to amplify the V4 region of the 16S rRNA gene. The polymerase chain reaction products are then retrieved after separation on an agarose gel using electrophoresis, excised from the gel, and subsequently purified with a QIAquick Gel Extraction Kit (Qiagen, Germantown, MD, USA). The Illumina MiSeq DNA sequencing platform is used to sequence 250 base paired-end kits.

Microbiome analyses will be performed using the Quantitative Insights into Microbial Ecology bioinformatics software and QWRAP program as previously described [18]. Briefly, quality assessment and filtering of low-quality data will be performed using the FASTQC and FASTX toolsets, respectively. A combination of tools within the Quantitative Insights into Microbial Ecology software suite will be utilized for clustering reads into operational taxonomy units (uclust), taxa assignment (RDP classifier using the Greengenes 16S rDNA database) and, as necessary, alignment and phylogenetic inference (using PyNAST and FastTree). These procedures will allow us to quantitatively assess the microbiome population down to the genus, if not species, level. For comparative analyses, indices of alpha (Chao1, Observed species, Phylogenetic distance, Simpson’s index and Shannon’s index) and beta diversity (Bray–Curtis dissimilarity, unweighted UniFrac and weighted UniFrac) will be computed [18].

### Procedures to quantify serum biomarkers that may be linked to improvements in neurological recovery and functional independence

#### Sample processing

Serum samples are processed using disposable affinity-depletion cartridges (NorGen Biotek Corp.) that remove the major serum proteins albumin, α-antitrypsin, transferrin and haptoglobin [32]. Protein samples are evaporated and resuspended in 6 M urea, 100 mM Tris buffer at 10 mg/ml. Aliquots of the affinity-depleted serum are reduced using dithiothreitol (25 mM) at 50°C for 30 min followed by alkylation of free thiol groups with iodoacetamide (55 mM) for 30 min in the dark at room temperature. Solutions are then diluted 1/10 in double-distilled water (ddH_2_O) and overnight digestion is carried out using mass spectrometry (MS)-grade trypsin (0.2 μg/μl). The digests are evaporated to dryness in a Speedvac and then resuspended in 50 μl ddH_2_O with 0.1% formic acid.

#### Targeted protein analysis

Peptides representing fibrinogen, extracellular signal-regulated kinase 1/2, CD11b/CD18 integrin receptor and epidermal growth factor are selected from either preliminary data (fibrinogen) or using Skyline, a targeted proteomics software tool [33]. Predicted product ions from each peptide are used to set up a multiple reaction monitoring liquid chromatography tandem MS (LC-MS/MS) assay carried out on a SCIEX 6500 Qtrap using microflow LC. This instrument is very sensitive and is capable of detecting peptides in the amol range. The tryptic peptides are resolved on a 5–50% linear gradient of acetonitrile in 0.1% formic acid mobile phase before entering the electrospray ionization (ESI) interface of the mass spectrometer. Synthetic peptides will be used to obtain quantitative data. To obtain absolute quantitative data on the selected peptide(s), ^13^C/^15^N-isotopically labeled versions of the peptide(s) will be prepared [34].

#### Protein library generation

An aliquot (5 μl) of each digest is loaded onto a Nano cHiPLC 200 μm × 0.5 mm ChromXP C18-CL 3-μm 120-Å reverse-phase trap cartridge (Eksigent, Dublin, CA, USA) at 2 μl/min coupled to an Eksigent 415 LC system autosampler. After washing the cartridge for 10 min with 0.1% formic acid in ddH_2_O, the bound peptides are flushed onto a Nano cHiPLC column (200 μm ID× 15 cm ChromXP C18-CL 3 μm 120 Å; Eksigent) with a 100-min linear (5–50%) acetonitrile gradient in 0.1% formic acid at 1000 nl/min using an Eksigent Nano1D + LC. The column then is washed with 90% acetonitrile 0.1% formic acid for 5 min and re-equilibrated with 5% acetonitrile 0.1% formic acid for 15 min. A SCIEX 5600 TripleToF mass spectrometer (SCIEX, Toronto, Canada) is used to analyze the protein digest. The ionization spray voltage is set at 2300 V and the declustering potential set at 80 V. The ionization spray and curtain gases are set at 10 psi and 25 psi, respectively. The interface heater temperature is 120°C. In each 1.25-s duty cycle, eluted peptides are subjected to a 250-ms time-of-flight survey scan covering a range of 400–1250 m/z to determine the top 20 most intense ions for MS/MS analysis. Product ion time-of-flight scans at 50 ms are carried out to obtain the tandem mass spectra of the selected parent ions over a m/z range of 400–1000. Spectra are centroided and de-isotoped by Analyst software, version 1.7 TF (SCIEX). A β-galactosidase trypsin digest is used to establish and confirm the mass accuracy of the mass spectrometer. The MS/MS data are processed to provide protein identifications using an in-house Protein Pilot 4.5 search engine (SCIEX) using the UniProt *Homo sapiens* protein database and a trypsin digestion parameter. Proteins are included in the SWATH (sequential window acquisition of all theoretical mass spectra) library on the criteria of having at least two peptides detected with a confidence score of 95% or greater using the paradigm method imbedded in the Protein Pilot software.

#### SWATH-MS analysis

Individual samples are analyzed by the same nanoLC-ESI-MS/MS method described above. SWATH data [35] are collected in 1.8-s duty cycles—a 200-ms time-of-flight survey scan from m/z 400–1250 followed by 32, 50-ms successive tandem mass spectra using 25 m/z mass windows. The MS/MS data are deconvoluted and processed using PeakView™ 1.2 with the SWATH application (SCIEX). This software uses a pregenerated protein identification library to construct individual peptide signatures with fragmentation patterns after analyses for protein identifications. In addition, the areas of the peptide peaks in the MS/MS spectra are used for protein quantification. Identification of proteins associated with the phenotypes being studied will be carried out by univariate (volcano plots) and multivariate (principal components and partial least squares-discriminant analysis) analyses and associated heat-maps.

### Power calculations

Power calculations were performed using nQuery Advisor + nTerim 3.0, and assume a two-sided statistical test and a significance level of 5%. We obtained estimates of the standard deviation for the motor score of 23.5 and for the light touch score of 33 (both based on our preliminary data). With a final sample size of 24 participants per group, and also assuming a two-group *t* test and the prior assumptions, we have 80% power to detect between-group differences of 19.5 in the motor score and 27.3 in the light touch score as being statistically significant. With a final sample size of 24 participants per group, and assuming a paired *t* test and the prior assumptions, we have 80% power to detect within-group changes of 14.1 in the motor score and 19.8 in the light touch score as being statistically significant. All of these differences are approximately at the same levels as those that Kramer et al. detected as being statistically significant and clinically meaningful [36]. We believe that these estimates are conservative since we are performing our primary statistical analyses for between-group and within-group comparisons simultaneously using statistical methods that are more sophisticated than those that are assumed here. Given our history in SCI patient recruitment and the large SCI patient base at the UAB SRC, we fully expect to meet our recruitment goal.

### Randomization and blinding

Randomization is performed using the block randomization method, with a block size of four (study statistician). A randomization list is generated, and the random assignments placed into closed envelopes. Each study participant opens one of these envelopes to learn of their group assignment. Study patients will inevitably know their group assignment as we are limited by the difficulties of inadequate masking of the ketogenic diet, which is very restrictive and requires avoidance of usual foods like bread, pasta, rice, potatoes and a wide variety of fruits. In order to avoid a potential placebo effect or a participant biasing results due to knowledge of their diet, during the consenting process we simply explain that the study is designed to examine the impact of KD and SD on outcomes. In addition, individuals performing clinical and laboratory tests and the study statistician were blinded to the study interventions.

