**Methods/design:**

In a single-masked, longitudinal, randomized, parallel-controlled study, a total of 60 eligible, acutely traumatic spinal cord injured (cervical 5 to thoracic 12) participants ranging in age from 18 to 60 years with American Spinal Injury Association impairment scale (AIS) grades A–C (AIS-A, sensorimotor complete; AIS-B, sensory incomplete/motor complete; and AIS-C, nonfunctional motor incomplete) are being enrolled. Neurological and functional examinations, resting energy expenditure, blood, urine, and stool collections, and protein analyses related to neurological recovery will be performed within 72 h of injury (baseline measure) and repeated after 5 weeks of KD or SD (discharge measure). We anticipate a completion rate of 80% with a total of 48 participants.

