## Research methods/design

### Study design and participants

In a single-masked, longitudinal, randomized, parallel-controlled study design, eligible participants or legally authorized representative (if the participant is under mechanical ventilation) who provide informed consent to the principal investigator (PI) or assigned study coordinator are randomly assigned into a KD intervention group or an SD control group in a 1:1 ratio. Block randomization method with a block size of four is performed by the study statistician. A randomization list is generated, and the random assignments are placed into closed envelopes. All nurses performing blood draws, core facilities and research staff (technicians, students and trainees) analyzing the primary outcomes are blinded to group assignment. A Standard Protocol Items: Recommendations for Interventional Trials (SPIRIT) schedule is presented in Fig. 2 and the SPIRIT checklist is shown as Additional file 1. Outcome measures are performed at three time points: at baseline within 72 h of injury, before discharge from the acute care unit to the rehabilitation hospital, and at discharge from the rehabilitation hospital. Neurological examination via International Standards for Neurological Classification of SCI (ISNCSCI), commonly referred to as the American Spinal Injury Association Impairment Scale (AIS), electrical perception thresholds (EPTs) [23], functional examinations via the Spinal Cord Independence Measure (SCIM) [24, 25], resting energy expenditure (REE) and blood collection (for metabolic, targeted proteomics and safety outcomes) are performed within 72 h of injury, prior to starting enteral feeding (baseline measure). Following acute care, patients are transferred to the University of Alabama at Birmingham (UAB) Spain Rehabilitation Center (SRC) for inpatient rehabilitation care with an average length of stay of 20 days for patients with acute SCI. Accordingly, subsequent examinations are performed prior to transfer to the SRC (rehabilitation measure) and discharge from the SRC at week 5 (discharge measure). A summary of the data collection schedule for the outcomes is shown in Fig. 2, and the flow diagram for the overall study design is shown in Fig. 3.

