### Recruitment

Participants are recruited from the UAB Hospital Trauma, Burns, and Surgical Critical Care (Acute Care) Unit. The PI is responsible for participant recruitment and trial coordination. Screening for the target participant pool is conducted by the UAB Emergency Medicine Research Assistance program. Participants are compensated US$100 for their time.

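### A fixed, published block size of four at one unmasked site leaves up to a third of allocations predictable, and the statistician who randomizes is also declared blinded

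*Protocol article*

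**What the plan says.** All references are to the protocol article.

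- **Method.** Randomization and blinding: "Randomization is performed using the block randomization method, with a block size of four (study statistician". Study design and participants agrees: "Block randomization method with a block size of four is performed by the study statistician". Consenting patients "are randomly assigned into a KD intervention group or an SD control group in a 1:1 ratio". No stratification of the randomization is described.
- **Concealment and unmasking.** Assignments are placed in closed envelopes. "Each study participant opens one of these envelopes to learn of their group assignment". Randomization and blinding accepts that patients cannot be masked to the diet.
- **Recruitment.** It takes place at one hospital unit, and "The PI is responsible for participant recruitment and trial coordination". Consent is given to the PI or a study coordinator.
- **Who is blinded.** Study design and participants lists nurses drawing blood, core facilities and research staff analyzing primary outcomes. The section on functional independence adds the examiners. Randomization and blinding says that "individuals performing clinical and laboratory tests and the study statistician were blinded to the study interventions". The recruiting PI and the coordinator are on none of these lists.
- **Statistician's other duties.** Under Data management, the study statistician checks the quality of the database periodically and shares the final data check.

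**The concern.** With one fixed block size, a run of known assignments can reveal the next one. Here the size is published while enrollment is open, there is one recruiting unit, and each assignment becomes visible once the patient starts a clearly different diet. Someone involved in recruitment could therefore know some allocations before approaching the next patient. Prognosis or willingness could then influence who is offered which slot. The planned ANCOVA adjusts for measured baseline values, age and sex, but not for unmeasured prognosis.

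The examiner blind matters too. It is the main protection for the motor, sensory and Spinal Cord Independence Measure (SCIM) outcomes when participants know their diet, and small fixed blocks can weaken it.

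Separately, one role is given the randomization and declared blinded in the same paragraph. No second statistician, independent list holder or coded list is described to reconcile the two.

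**Working it through.** **Inputs.** Block size 4 and 1:1 allocation come from Study design and participants and from Randomization and blinding. The abstract gives "a total of 60 eligible, acutely traumatic spinal cord injured" participants, and "We anticipate a completion rate of 80% with a total of 48 participants".

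**The plan's own figures.** The article gives no predictability figure. Its sample size is consistent: 60 × 0.80 = 48. Its power statement also reproduces: 24 per group, a difference of 19.5 and SD 23.5 give 80.3% by the exact noncentral t, against 80% stated. Neither is affected by this point. Sixty participants make 60 / 4 = 15 blocks.

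**Certain allocations.** A block holds two KD and two SD places, so there are 4! / (2! × 2!) = 6 equally likely sequences. An allocation is certain once one arm's two places are used.

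| Position in block | Chance the allocation is already certain | Chance the best guess is right |
|---|---|---|
| 1 | 0 | 1/2 |
| 2 | 0 | 2/3 |
| 3 | 1/3 | 1/3 × 1 + 2/3 × 1/2 = 2/3 |
| 4 | 1 | 1 |

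- Certain per block: 0 + 0 + 1/3 + 1 = 1.333, and 1.333 / 4 = 33.3%.
- Equivalent count: four of the six sequences have one certain allocation and two have two, so (4 × 1 + 2 × 2) / 6 = 1.333.
- Over 15 blocks: 15 × 1.333 = 20 of 60 expected. The minimum is 15, because every fourth allocation is fixed. The count is 15 + Binomial(15, 1/3), with a central 95% range of 17 to 24.
- Best guess (the arm with more places left): (1/2 + 2/3 + 2/3 + 1) / 4 = 70.8%, against 50% with no information.

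**Examiner.** If one patient's diet becomes known, three places remain in that block: one in the same arm and two in the other. Each other patient in the block then has a 2/3 chance of being in the opposite arm. Certainty about another patient needs two known patients in the same arm, or three known patients in all.

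**Varying block sizes (illustrative).** The article does not propose these. In 1,500 simulated lists of 60 per set, the recruiter knows the set of sizes and every earlier allocation:

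| Block sizes | Certain | Best guess right |
|---|---|---|
| Fixed 4 | 33.3% | 70.8% |
| 4, 6 | 5.5% | 69.1% |
| 2, 4, 6 | 3.9% | 70.1% |
| 4, 6, 8 | 2.2% | 68.0% |

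With 4, 6 and 8, the certain allocations fall from 20 to about 0.022 × 60 = 1.3 patients.

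**Statistician.** Two sections assign the block randomization to the study statistician, and Randomization and blinding then calls that role blinded. Data management has the same role checking data during the trial. The statements could agree if another person held the list or if its arms were coded, but the article says neither.

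**The case against.** Several points on the other side are fair.

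- **The third is a ceiling.** It needs envelopes used in list order, known block boundaries and a recruiter who knows all earlier allocations. The article says only that each participant opens one envelope. Free picking would weaken prediction, but it would also lose the block balance, so the order of use needs fixing either way.
- **There is limited room to act on foreknowledge.** An emergency-department research program screens around the clock, a coordinator may take consent, and baseline must fall within 72 h of injury. Assignment after consent is already stated. These points reduce the opportunity for steering but do not remove it.
- **Article-level detail.** Envelope numbering and list custody may be in the full protocol, and their absence here is no finding. The stated fixed block size and the two conflicting statements remain.
- **Coded data.** Records carry four-digit identifiers with the identity keys held separately, so producing a list need not reveal which record has which arm. This could reconcile the statistician wording, but the article does not say so.

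A reader might infer more than the text supports: that selection bias occurred, that one leaked diet tells the examiner the other arms in the block, that the statistician who randomizes also runs the final analysis, or that varying the block size would nearly abolish predictability. The article contains no evidence of biased enrolment. One leak gives 2/3, not certainty, and nothing says the examiner knows the enrolment order. No section says who runs the analysis; only the data checks are assigned. Best-guess success stays near 68% with blocks of 4, 6 and 8.

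**Conclusion.** The point holds as a potential weakness together with a conflict in the text. With a fixed, disclosed block of four, up to 33.3% of allocations (20 of 60 expected, at least 15) can be known in advance, and best-guess success is 70.8%. This assumes list-order use, known block boundaries and known earlier assignments. The single site and visibly different diets make the last of these plausible for the PI and coordinator. Examiner blinding may be weakened but is not shown to fail.

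The article both gives the study statistician the randomization and declares that role blinded. As written the statements conflict, and the claimed masking is unsupported unless a separation of duties is described. The block arithmetic is exact; how far anyone could use it depends on conduct that the article does not describe.

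**What to change.** 1. For remaining participants, starting at a block boundary, use randomly varying block sizes (for example 4, 6 and 8) that are not disclosed to recruiting staff.
2. Use sequentially numbered envelopes, opened in order, and only after consent and the baseline neurological, electrical perception threshold and SCIM assessments are recorded. Varying the block size does little to the best-guess rate, so this step carries much of the protection.
3. Have the list generated and held by someone at the institution who does no data checking or analysis, and give the study statistician arm-coded data.
4. If step 3 is not possible, or no slots remain, correct or delete the statement that the study statistician is blinded. Enrollment was expected to end in December 2023, and the article does not show whether slots remain.

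The cost is protocol wording and a regenerated list for the open slots. The statistical downside is a possible end-of-trial imbalance of up to about 4 patients, if the trial stops partway through a block of 8. A switch in mid-block could add 2 more, hence the block-boundary start. Sample size and power do not change.
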